Progranulin is a secreted glycoprotein associated with the regulation of lysosome function and inflammation ([Chitramuthu et al 2017](#)). Progranulin is broadly expressed in the CNS and periphery in a variety of cell types ([Chitramuthu et al 2017](#)). Progranulin expression has been reported to be upregulated in certain tumors and tumor cell lines ([Serrero 2003](#); [Chitramuthu et al 2017](#)). Furthermore, overexpression of PGRN in vitro, in tumor cell lines or primary tumor cells, has been reported to increase certain tumorigenic properties in some contexts ([He et al 2002](#); [Chitramuthu et al 2017](#)) but not in other contexts

([Matsumura et al 2006](#)). In contrast to these studies, overexpression of PGRN in vivo has been reported by several groups using AAV or lentiviral transduction and transgenic mouse approaches, without findings of tumor formation ([Tao et al 2012](#); [Altmann et al 2016](#); [Arrant et al 2018](#)). Furthermore, direct intravenous administration of PGRN in vivo has not been reported to be associated with tumorigenesis ([Tang et al 2011](#)). Consistent with these findings, the Sponsor's in vivo studies using PR006A to overexpress PGRN in mouse models or normal NHPs have not revealed tumorigenic potential.

Based on the above analysis, an increased risk of malignancy is considered by the Sponsor to be unlikely in the context of PR006A administration. Patients with a history of cancer within 5 years of Screening or current presence of pre-cancerous lesions will be excluded from study participation, with the exception of fully excised prostate carcinoma in situ and fully excised nonmelanoma skin cancers that have been stable for at least 6 months. Patients will also be required to have up to date age- and gender-appropriate cancer screenings, completed as per the Investigator's judgment and local standard of care, prior to inclusion/exclusion Screening. Additionally, the occurrence of malignancy at any point after gene transfer that is judged as at least probably related to PR006A per the Sponsor's final causality assessment is one of the study stopping rules ([Section 4.2.4](#)).

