### **4.2.4 Study Stopping Rules**

Each patient will receive only 1 dose of PR006A once during the course of the study; hence, stopping rules apply only during the Screening Period. Patients who have been dosed with PR006A will be followed to the end of the study as per protocol.

If any one of the following criteria are met, PR006A dosing will be paused and further enrollment across all study sites will be halted until the iDMC evaluates all available study data and makes a recommendation:

- More than  $5 \times$  ULN increase in ALT, AST, or both in any patient after PR006A administration that is not manageable by corticosteroid treatment implemented according to AASLD guidelines ([Manns et al 2010](#)).
- The occurrence of 2 or more of any 1 of the following treatment-emergent AEs (TEAEs)/SAEs (not 2 single occurrences of different AE/SAE):
  - Subarachnoid hemorrhage, cerebral macrohemorrhage
  - Grade 3 and/or 4 allergic reactions, hypersensitivity reactions, cytokine release reactions
  - Persistent neurological symptoms at least possibly attributable to the ICM investigational product administration procedure
  - CNS infections (e.g., meningitis, encephalitis)
  - Seizures, stroke, or acute paralysis
- More than 1 patient experiences any Grade 3 or higher AE that is judged as definitely, probably, or possibly attributed to PR006A.
- More than 1 Grade 3 or higher SAE that may or may not be potentially related to PR006A and that poses either an immediate risk to the patient's health or is likely to adversely affect the patient's long-term health.
- Death of a patient, after having received PR006A, that is judged as definitely, probably, or possibly attributed to PR006A. The study will be temporarily stopped in order to undergo review by the institutional review board (IRB)/independent ethics committee (IEC), iDMC, and other health authorities.
- The occurrence of a malignancy at any point after gene transfer that is judged per the Sponsor's final causality assessment as related to PR006A.

The study may be terminated if one or more of the following criteria are met:

1. The Sponsor decides to terminate the study based upon an assessment of safety.
2. The Sponsor decides to terminate the study for administrative reasons.

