### **6.2.1.5 Suspected Adverse Reactions/Adverse Reactions**

The following AEs will be considered as ARs:

- All AEs occurring within 1-month post-PR006A administration procedure
- All AEs assessed as at least possibly related to the injection procedure or to investigational product treatment by the Investigator or Sponsor
- All AEs for which the Investigator's causality assessment is missing or indeterminate

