### **6.2.1.8 Suspected Unexpected Serious Adverse Reactions**

A suspected unexpected serious AR (SUSAR) is defined as any suspected AR to study treatment that is both serious and unexpected.

The event(s) must meet all of the following criteria:

- Suspected AR
- Serious
- Unexpected
- Assessed as at least possibly related to study treatment or if Investigator's causality assessment is missing or indeterminate

The Sponsor will promptly evaluate all SUSARs against cumulative product experience to identify and expeditiously communicate possible new safety findings to Investigators, IRBs/IECs, and applicable health authorities based on applicable legislation.

To determine reporting requirements for single AE cases, the Sponsor will assess the expectedness of these events using the IB.

Reporting requirements will also be based on the Investigator's assessment of causality and seriousness, with allowance for upgrading by the Sponsor as needed.

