#### **6.2.1.10 Assessment of Causality**

The Investigator's assessment of an AE's relationship to investigational product is part of the documentation process, but it is not a factor in determining what is or is not reported in the study. If there is any doubt as to whether a clinical observation is an AE, the event should be reported.

The relationship or association of the investigational product or the ICM administration of the investigational product in causing or contributing to the AE will be characterized using the following classification and criteria:

- **No** (unrelated, not related, unlikely to be related) – The time course between the administration of investigational product and the occurrence or worsening of the AE rules out a causal relationship and another cause (concomitant drugs, therapies, complications, etc.) is suspected.
- **Yes** (possibly, probably, or definitely related) – The time course between the administration of the investigational product and the occurrence or worsening of the AE is consistent with a causal relationship should be considered at least possibly related to investigational product or investigational product administration procedure. This is defined as all AEs that begin during or within 1 month following investigational product administration, plus all AEs regarded by the Investigator or Sponsor as at least possibly related to investigational product or investigational product administration procedure, plus all AEs for which the Investigator's causality assessment is missing or indeterminate.

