Based on the above analysis, an increased risk of malignancy is considered by the Sponsor to be unlikely in the context of PR006A administration. Patients with a history of cancer within 5 years of Screening or current presence of pre-cancerous lesions will be excluded from study participation, with the exception of fully excised prostate carcinoma in situ and fully excised nonmelanoma skin cancers that have been stable for at least 6 months. Patients will also be required to have up to date age- and gender-appropriate cancer screenings, completed as per the Investigator’s judgment and local standard of care, prior to inclusion/exclusion screening. Additionally, the occurrence of malignancy at any point after gene transfer that is

judged as at least probably related to PR006A per the Sponsor's final causality assessment is one of the study stopping rules ([Section 4.2.4](#)).

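### The malignancy stopping rule carries two causality thresholds: related in Section 4.2.4, at least probably related in Sections 1.3 and 6.2.2.5

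*Protocol*

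**What the plan says.** Section 4.2.4 (Study Stopping Rules) lists the criteria that pause dosing and halt enrollment at all sites until the iDMC has reviewed the data. Its last criterion is a malignancy, at any time after gene transfer, judged in the Sponsor's "final causality assessment as related to PR006A". It gives no degree of relatedness.

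Two other sections restate this criterion and cite Section 4.2.4 as its source:

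- Section 1.3 (Risk/Benefit) names as a stopping rule "the occurrence of malignancy at any point after gene transfer that is judged as at least probably related to PR006A", again by the Sponsor's final assessment.
- Section 6.2.2.5 (Risks Associated with GRN Expression) uses the same threshold: "judged as at least probably related to PR006A per the" Sponsor's final assessment.

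The general causality definitions draw the line lower:

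- In Section 6.2.1.10 the scale is Yes or No, and Yes covers "possibly, probably, or definitely related".
- Section 6.2.1.5 counts as adverse reactions "All AEs assessed as at least possibly related to the injection procedure or to investigational product treatment by the Investigator or Sponsor".
- The SUSAR criteria in Section 6.2.1.8 include "Assessed as at least possibly related to study treatment".

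**The concern.** A stopping rule is useful because its trigger is fixed before an event occurs. Here the protocol states one trigger at two levels. The difference falls on the middle category, a malignancy judged possibly but not probably related.

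That category is a realistic one in this trial. Section 1.3 reports that progranulin overexpression increased some tumorigenic properties in vitro in some contexts, although the Sponsor considers an increased risk from PR006A unlikely. Sections 1.3 and 6.2.2.2 also list malignancies and lymphomas among the risks of the immunosuppressive regimen, which every patient receives. With two candidate contributors, an assessor could well stop at possibly related.

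At stake is whether dosing in a first-in-human gene therapy study pauses automatically after such a case, or continues while the meaning of the rule is debated.

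**Working it through.** The plan states no figure to reproduce on this point. The check compares the texts, and one short calculation shows how long the conflict can act.

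**Step 1. Same rule, same assessor.** All three sections concern a malignancy after gene transfer and rely on the Sponsor's final causality assessment. Sections 1.3 and 6.2.2.5 both refer to Section 4.2.4. They therefore report that rule and do not set up a second one.

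**Step 2. Decision by causality judgement**, reading related as Section 6.2.1.10 defines it:

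| Sponsor's final judgement | Section 4.2.4 | Sections 1.3 and 6.2.2.5 |
|---|---|---|
| Definitely related | Pause | Pause |
| Probably related | Pause | Pause |
| Possibly related | Pause | No pause |
| Unlikely or unrelated | No pause | No pause |

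The texts differ in the third row only.

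**Step 3. Does another criterion in Section 4.2.4 catch one non-fatal, possibly related malignancy?**

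- Liver enzyme criterion: does not concern malignancy.
- Listed events, two or more of one type: malignancy is not on the list.
- Grade 3 or higher AEs: "More than 1 patient experiences any Grade 3 or higher AE that is judged as definitely, probably, or possibly attributed to PR006A". One patient is not enough.
- Grade 3 or higher SAEs: "More than 1 Grade 3 or higher SAE that may or may not be potentially related to PR006A", with a further condition on the health risk. One event is not enough.
- Death: not met, because the case is non-fatal.

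No other automatic criterion applies to the case taken alone.

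**Step 4. How long the conflict can act.** Inputs: 3 cohorts (Section 7.4); at least 8 weeks between the first and second patients and at least 8 more before the remaining three (Section 3.1.1); the next cohort may open when the remaining patients of the current one may be dosed (Section 3.1.1).

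Earliest dosing weeks:

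- Cohort 1: 0, 8, 16
- Cohort 2: 16, 24, 32
- Cohort 3: 32, 40, 48

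Minimum span from first to last dose = 3 × (8 + 8) = 48 weeks, if all cohorts open and fill. The same span applies to every stopping rule. It shows the period of exposure to the conflict and says nothing about how likely a case is.

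**The case against.** The best defence is that Section 4.2.4 leaves related undefined for this rule and the other two sections supply the missing degree, so the three can be read together. Some context supports this. The Grade 3 or higher AE rule and the death rule in the same list spell out that possibly counts, and the malignancy rule does not, so the difference may be deliberate. The definitions in Sections 6.2.1.5, 6.2.1.8 and 6.2.1.10 serve AE documentation and reporting. The Yes class in Section 6.2.1.10 also takes in, by default, AEs that begin within 1 month of administration and AEs with a missing or indeterminate Investigator assessment. That fits poorly with a considered final assessment by the Sponsor.

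This reading is possible but weak. The only causality scale the protocol defines puts possibly on the related side, Sections 6.2.1.5 and 6.2.1.8 draw the same line, and Sections 6.2.1.5 and 6.2.1.10 name the Sponsor as an assessor. If the stricter threshold was intended, the operative list does not say so. If it was not, two sections misreport the rule. The text needs correcting in either case.

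Two parts of the objection stand. First, other safeguards exist: SAE reporting within 24 hours, prompt Sponsor evaluation of SUSARs, the iDMC's power to recommend modification or termination, and the Sponsor's right to stop. A malignancy that is itself a qualifying Grade 3 or higher SAE would also need only one more such event to trigger the SAE rule. These limit the harm, but reporting does not pause dosing and the other powers are discretionary, whereas a stopping rule is automatic. Second, consistency alone could also be reached by writing at least probably into Section 4.2.4, so the choice of threshold needs its own justification.

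**Conclusion.** The contradiction is real. For one non-fatal malignancy judged possibly related, Section 4.2.4 pauses dosing and Sections 1.3 and 6.2.2.5 do not. This rests on reading related as Section 6.2.1.10 defines it, which is the natural reading but is not spelled out in Section 4.2.4.

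The impact is low to moderate. The circumstance is narrow, and the result is a pause for iDMC review while patients remain to be dosed. It should still be corrected, because it leaves a first-in-human safety trigger open to argument after a case has occurred. No malignancy rate is given in the protocol and none is assumed.

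**What to change.** In Section 4.2.4, state the malignancy criterion as at least possibly related to PR006A in the Sponsor's final causality assessment, and use the same threshold in Sections 1.3 and 6.2.2.5. This keeps the meaning of the operative section on the protocol's own scale and matches the neighbouring Grade 3 or higher AE and death rules. If the Sponsor does intend at least probably, Section 4.2.4 must say so explicitly and should explain why malignancy has a higher threshold than those rules.

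The change is to wording in three sections, with no effect on sample size, visits or analyses. Its cost is that a malignancy judged only possibly related will pause dosing for an iDMC review that may prove to be a false alarm.

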## 5 Study Treatments

### 5.1 Method of Assigning Patients to Treatment Groups

This is an open-label study. No randomization or blinding will be performed.

### 5.2 Treatments Administered

PR006A is an investigational AAV9 gene therapy drug product transducing wildtype *GRN* gene. Please refer to the IB and Pharmacy Manual for further details regarding the study treatment.

### 5.3 Identity of Investigational Product

PR006A is an investigational gene therapy that utilizes an AAV9 viral vector to deliver DNA encoding wildtype *GRN*, the gene encoding PGRN, to a patient's cells.

██████ escalating-dose cohorts are planned ( $3.5 \times 10^{13}$  vg,  $7.0 \times 10^{13}$  vg, ██████ of PR006A).

Refer to the IB for further details related to PR006A.

### 5.4 Management of Clinical Supplies

#### 5.4.1 Investigational Product Packaging and Storage

PR006A concentrate for the low, mid, ██████ doses will be supplied as a frozen solution for injection in single-use polypropylene vials or Type I, Class A glass serum vials and stored in individually labeled vials at  $-60^{\circ}\text{C}$  or lower.

Details regarding packaging and storage are provided in the Pharmacy Manual and the IB.

#### 5.4.2 Investigational Product Preparation and Dispensing

PR006A doses are prepared by dilution, if necessary, using the formulation buffer and will be mixed thoroughly prior to the administration, while maintaining sterile conditions. Dose preparation will be conducted by a trained pharmacist/medical technologist in accordance with the Pharmacy Manual.

## **5.5 Investigational Product Administration**

### **5.5.1 Immunosuppressant Administration**

#### **5.5.1.1 Corticosteroid Administration**

Subjects will receive a loading dose of methylprednisolone 1 g IV pulse on Day 0. Prednisone at a dose of 30 mg/day will be given orally as concomitant medication from Day 1 for 14 days, which will be then tapered over the ensuing 7 days. At the Investigator's discretion, higher doses or a longer taper of corticosteroids may be used.

Mitigation of risks associated with use of corticosteroids, including monitoring for AEs that may be related to corticosteroid use are described in [Section 6.2.2.2](#).

#### **5.5.1.2 Sirolimus Administration**

Patients will receive a sirolimus oral loading dose of 6 mg at Day -1. Subsequent sirolimus maintenance dose of 2 mg will be adjusted to maintain serum trough levels of 4 ng/mL (range 2 to 8 ng/mL) until the Month 3. Sirolimus will be subsequently tapered during the subsequent 15 to 30 days. Trough levels will be collected prior to administration of the sirolimus dose for each visit as presented in Schedule of Events (main study period). All sirolimus doses will be captured in the eCRF.

All patients and caregivers should be provided with a current version of the local manufacturer's medication guide, including instructions for use.

#### **5.5.1.3 Immunosuppression Monitoring Criteria**

In addition to monitoring sirolimus trough levels, the Investigator should evaluate patient's clinical status, lab findings and potential AEs.

Consideration should also be given to the need to increase doses of the immunosuppressant agent, prolong the tapering regimen, add a third agent or re-initiate treatment based on clinical signs or symptoms consistent with an immune response, including:

- Asymptomatic pleocytosis with WBC > 30 mm^3 and/or high CSF protein (> 70 mg/dL)

- CSF pleocytosis and/or increased protein accompanied by clinical symptoms (including decompensation of underlying FTD symptoms)
- Emergence of sensory symptoms based on neurological examination and/or TNAS.
- ALT and/or AST elevation  $>5 \times$  ULN in conjunction with hepatitis symptoms (e.g., jaundice, fatigue)
- ALT and/or AST elevation  $>10 \times$  ULN irrespective of the presence or absence of clinical symptomatology

The Investigator should consider implementing a longer prednisone taper over an additional 4 weeks in patients presenting with ALT and/or AST  $>3 \times$  ULN at the end of the initial 14-day taper. In case of AST/ALT elevations refractory to prednisone treatment, the Investigator should seek expert advice from a hepatologist.

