### 1.2.3 Rationale for Staggering of Patient Enrollment

Based on available nonclinical data, no specific safety signals are anticipated in humans, other than potential risk for liver enzyme elevations related to AAV9-capsid-specific T-cell responses observed in previous human studies with AAV9 vectors ([Mendell et al 2017](#)). In order to monitor for any unexpected safety events in humans, including but not limited to potential transitory liver enzyme elevations, in each cohort, enrollment will be staggered by at least 8 weeks between the first 2 patients and then at least 8 weeks between the second patient and the remaining 3 patients of the cohort to permit review of safety, tolerability, immunogenicity, and, to the extent available, efficacy by the iDMC, who will ultimately provide a recommendation on further dosing. This 8-week monitoring period was established to capture the reported time-frame for liver enzyme elevations caused by T-cell responses, which were observed at approximately 3 weeks post-dosing ([Mendell et al 2017](#)). It also ensures the iDMC will have appropriate biomarker and safety data from the Month 2 visit to make their recommendation. Since presumably, CSF inflammatory changes occur between 1 and 2.5 months post-dosing, at least 8 weeks after the second staggered patient is dosed in Cohort 1, the iDMC will review all available safety, tolerability, immunogenicity, and, to the extent feasible, efficacy results from the first 2 patients in this cohort (dosed in a staggered manner). At the recommendation of the iDMC, the Sponsor will decide whether to dose the remaining 3 patients in Cohort 1 (low dose) without staggering and in parallel begin staggered enrollment in the mid-dose cohort (Cohort 2).

Escalation to the mid-dose ( $7.0 \times 10^{13}$  vg) [REDACTED] level cohorts will be based on iDMC recommendation, assessments of safety and biomarker data from the clinical PR006A low- and mid-dose cohorts, as well as technical feasibility (e.g., the ability to obtain sufficient concentrations of PR006A within the limitations of injectate volume).

Once enrollment of at least 2 patients in the low-dose cohort is complete and at least 8 weeks have elapsed after the second patient is dosed, the iDMC will review cumulative tabulated

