##### **3.1.1 Year 1**

Fifteen patients will be administered a one-time dose of PR006A, suboccipitally injected into the cisterna magna by an interventional radiologist or neurosurgeon.

In each cohort, enrollment will be staggered by at least 8 weeks between the first 2 patients and then an additional 8 weeks between the second patient and the remaining 3 patients of the cohort to permit review of safety, tolerability, immunogenicity, and, to the extent available, efficacy by the iDMC, who will ultimately provide a recommendation on further dosing. At least 8 weeks after the second staggered patient is dosed in Cohort 1, the iDMC will review all available safety, tolerability, immunogenicity, and, to the extent feasible, efficacy results from the first 2 patients in this cohort (dosed in a staggered manner). At the recommendation of the iDMC, the Sponsor will decide whether to dose the remaining 3 patients in Cohort 1 (low dose) without staggering and in parallel begin staggered enrollment in the mid-dose cohort (Cohort 2).

Cohort 2 will enroll 5 patients to receive the mid-dose ( $7.0 \times 10^{13}$  vg) of PR006A, and

[REDACTED]. The design for Cohorts 2 [REDACTED] enrollment is the same as for Cohort 1.

If a decision is made to not open or to limit enrollment into a cohort (i.e., Cohort 2 and/or [REDACTED] due to safety or tolerability reasons, the unenrolled subjects may be re-allocated to a lower dose level cohort.

One loading dose of 6 mg oral sirolimus will be administered at Day -1, as well as a single dose of 1 g IV methylprednisone at Day 0. A concomitant maintenance dose of 2 mg/day sirolimus will be administered orally for 90 days starting at Day 0 which will then be tapered over the ensuing 15 to 30 days. The maintenance dose is administered to achieve a trough sirolimus concentration of 4 ng/mL (range 2 to 8 ng/mL). One day after treatment with PR006A, patients will start prednisone 30 mg orally for 14 days, followed by a 7-day taper. At the Investigator's discretion, adjustments of dose and duration are permitted.

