#### **6.2.2.4 Risks Associated with AAV9-Based Therapy**

The viral capsid of AAV9 may trigger the innate and adaptive immune system. Overall, products (investigational and marketed) using the AAV9 vector have been safe and generally well tolerated in over 500 patients. Out of an estimated 21 clinical trials investigating AAV9-based gene therapies, 7 use an IT route of administration with approximately 60 patients having received an investigational therapy. The mode of administration via CSF is intended to minimize systemic exposure, but inevitably there will be some escape of virus out of the CSF into the blood. In clinical studies, gene therapy candidates using AAV9 have been generally well tolerated. Transient elevations in AST and/or ALT, which respond to corticosteroid treatment, have been reported ([Mendell et al 2017](#)).

Pleocytosis and increased protein in the CSF was observed in one patient dosed with PR001A (Prevail's AAV9-based gene therapy candidate delivering the GBA1 gene to subjects suffering from PD-GBA). Steroid-responsive CSF pleocytosis has been reported in another gene therapy trial utilizing AAV9 viral vector to deliver GAN gene to the patients suffering from giant axonal neuropathy (NCT02362438) ([Bharucha-Goebel et al, 2020](#)).

To mitigate the risk of potential capsid and other related immune reactions, the prophylactic course of immunosuppressive treatment (consisting of corticosteroids and sirolimus) should be followed as specified in the protocol. In cases of elevations of liver enzymes, inflammatory changes in the CSF or other suspected immune reactions to PR006A, higher doses, prolongation or re-initiation of immunosuppressive treatment may be considered at the discretion of the principal investigator. Risk mitigation for the immunosuppressive regimen is discussed in [Section 6.2.2.2](#).

While minimal axonal degeneration and gliosis limited to the dorsal funiculus as well as minimally increased cellularity in small clusters occurred in the DRG of few PR006A-treated NHPs, these findings were non-inflammatory, limited in their extent, and without clinical correlate, and therefore deemed non-adverse (PRV-2018-028). It is not predicted that the non-adverse findings in the NHPs will clinically translate to human patients. Notwithstanding, the protocol will exclude individuals with clinical evidence of peripheral symmetric sensory polyneuropathy and incidence of sensory symptoms will be monitored

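### The dosing-pause rules in Protocol 4.2.4 do not name non-infectious CSF inflammation, a recognised risk for which 5.5.1.3 sets limits but prompts only a treatment decision

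*Protocol*

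**What the plan says.** **The risk is recognised.** Section 1.2.3 presumes that "CSF inflammatory changes occur between 1 and 2.5 months post-dosing" and uses this to time the iDMC review. Section 6.2.2.4 reports that "Pleocytosis and increased protein in the CSF was observed in one patient dosed with PR001A", a sister AAV9 product of the sponsor, and mentions steroid-responsive pleocytosis in another AAV9 trial.

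**Limits are set.** Section 5.5.1.3 lists, among signs of an immune response, asymptomatic pleocytosis with WBC above 30 per mm³ and/or CSF protein above 70 mg/dL, and separately "CSF pleocytosis and/or increased protein accompanied by clinical symptoms (including decompensation of underlying FTD symptoms"). The response is "Consideration should also be given to the need to increase doses of the immunosuppressant agent", to taper more slowly, to add a third agent or to restart treatment. Sections 1.2.5 and 6.2.2.4 likewise leave this to the investigator's discretion.

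**Pause rules.** Under 4.2.4, dosing and enrolment stop at all sites until the iDMC has made a recommendation. The liver criterion acts on ALT and/or AST above 5 × ULN in any one patient if "not manageable by corticosteroid treatment implemented according to AASLD guidelines". The CNS bullet covers "CNS infections (e.g., meningitis, encephalitis") and needs two occurrences. A general rule applies when "More than 1 patient experiences any Grade 3 or higher AE that is judged as definitely, probably, or possibly attributed to PR006A". Another counts more than one Grade 3 or higher SAE that threatens the patient's health, whether or not related.

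**Dosing sequence.** After the iDMC review of patients 1 and 2 in Cohort 1, section 3.1.1 lets the sponsor dose the remaining 3 "without staggering and in parallel begin staggered enrollment in the mid-dose cohort". Later cohorts follow the same design.

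**The concern.** Two immune risks sit side by side in 5.5.1.3, liver enzyme elevation and CSF inflammation. The liver risk has its own pause rule in 4.2.4, triggered by one patient whose condition cannot be controlled. CSF inflammation has none: the nearest bullet is confined to infections and needs two of them. The protocol also does not state that the iDMC is told promptly when a patient meets the CSF criteria.

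The product is given once, cannot be withdrawn, and is in humans for the first time. Patients 3 to 5 of a cohort have no minimum interval between them, and the next dose level can open in parallel. At stake is whether the committee that advises on further dosing learns in time of an uncontrolled sterile CSF reaction, or of a run of moderate ones.

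**Working it through.** No sample size, power or error rate is involved. The check is to take each kind of CSF case through the 4.2.4 list as written.

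**Grading.** Severity follows CTCAE v5.0, which is not among the documents. On the fallback scale in 6.2.1.9 for unlisted terms, an asymptomatic finding is Grade 1, or Grade 2 if minimal intervention is indicated. A symptomatic case can be Grade 2. A case that indicates hospital admission is Grade 3.

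| Case | Rule in 4.2.4 that could apply | Pause? |
|---|---|---|
| ALT/AST above 5 × ULN, unmanageable, one patient (comparison) | Liver criterion | Yes |
| CSF limits exceeded without symptoms, any number of patients | None | No |
| Symptomatic, sterile, below Grade 3, two or more patients | Infection bullet does not apply; Grade 3 rules not reached | No, unless another named event occurs twice (for example persistent neurological symptoms attributable to the procedure) |
| One patient, Grade 3 or higher, refractory to immunosuppression | Related-AE rule needs more than one patient; SAE rule needs more than one SAE | No, unless a second qualifying event occurs in this or another patient |
| Grade 3 or higher and related, two patients | Related-AE rule | Yes |
| Related death | Death criterion | Yes |

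The second row is reasonable as it stands. The third and fourth rows are the gap.

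**Causality.** Sections 6.2.1.5 and 6.2.1.10 treat an AE as related by default if it begins within 1 month of administration, or if the causality assessment is missing or indeterminate. The presumed period for CSF inflammation starts at 1 month, so the related-AE rule will mostly depend on a judgement.

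**Who is exposed.** Section 7.4 gives 3 cohorts × 5 = 15 patients. Each cohort has 2 staggered and 3 unstaggered patients, so 3 × 3 = 9 of 15 are dosed after their cohort's review. A case first seen in patient 3, for example, could arise while patients 4 and 5, or patients in the next cohort, are still undosed. Whether any remain depends on recruitment speed, which the protocol does not give. If patients 3 to 5 are dosed close together, all may be treated before the first shows a reaction.

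**Other routes to the iDMC.** Sections 6.2.1.6 and 6.2.1.7 require SAE reporting within 24 hours, to the CRO and sponsor. No section requires prompt iDMC notification when a CSF criterion is met.

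**The case against.** The strongest reply is that this is an omission, not an error, and that other controls already cover much of it.

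- Section 6.5 requires clinically significant abnormal results to be recorded as AEs or SAEs, and 6.2.1.3 requires AEs found in any study data relevant to safety to be documented.
- A refractory case could readily be an SAE, through hospital admission or as an important medical event. It would then reach the sponsor within 24 hours and, if a SUSAR, be evaluated promptly and communicated to investigators, ethics committees and authorities.
- The sponsor may suspend enrolling cohorts in consultation with the iDMC, and the iDMC sees all available safety data after patient 2 of each cohort.
- Section 11.1.1 leaves details to an iDMC charter that is not shown and may contain a notification rule.
- The precedent cited from the giant axonal neuropathy trial responded to steroids.

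All of this stands, and it reduces the weight of the point. It does not remove it. These routes rely on discretion or lead to the sponsor, whereas 4.2.4 is the protocol's own list of mandatory pauses and treats the parallel liver risk differently. A charter may add notification, but the pause criteria are fixed in 4.2.4.

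Three stronger readings are not supported:

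- **That any single case short of death escapes 4.2.4.** The SAE rule counts events and the named-event list counts occurrences, so one patient with two qualifying events can trigger a pause.
- **That the iDMC is cut off from CSF data because Section 2 does not name CSF cell count, protein and glucose.** The synopsis lists them as safety variables and the iDMC receives all available safety data. Naming them is minor alignment.
- **That the harm or delay can be quantified.** The documents give neither a reaction rate nor a dosing calendar. Both 8-week gaps in a cohort are meant to permit iDMC review, so no fixed delay follows from the text.

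**Conclusion.** The point holds as a design choice worth reconsidering, not as a mistake or contradiction. Under 4.2.4 as written, two situations need not pause dosing: one CSF inflammation case refractory to immunosuppression without a second qualifying event, and repeated symptomatic sterile cases below Grade 3. They matter only while unstaggered patients, or patients in the next cohort, remain to be dosed. That group is limited to part of a small trial, and could be nobody if dosing is fast.

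The conclusion assumes that the bullet on infections excludes sterile meningitis and encephalitis, which is its plain meaning, and that the charter does not already require notification. If the charter does, only the missing pause criterion is left. Confidence is medium.

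**What to change.** 1. In 4.2.4, add a criterion parallel to the liver one: symptomatic, non-infectious CSF inflammation in any patient after PR006A that cannot be managed with immunosuppression. The liver criterion refers to a guideline for its treatment standard, so the new one needs a line saying what counts as unmanageable and who decides.
2. In 5.5.1.3 or 11.1.1, require prompt iDMC notification of any patient who meets either CSF criterion in 5.5.1.3, or cross-refer to the charter if it already says so. This covers repeated cases below Grade 3.
3. State that asymptomatic pleocytosis alone does not pause dosing.
4. As minor alignment, name CSF cell count, protein and glucose in the Section 2 safety list.

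The cost is wording, a few iDMC notifications and possibly a short pause while the committee reviews a refractory case. No new procedure is needed: these CSF measures are already planned, and the schedule of events allows unscheduled lumbar puncture.
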